### Treatment

According to the Chinese guidelines for the diagnosis and treatment of chronic stable angina [24], participants included in this trial will receive the standard conventional therapy as a basic treatment, including oral nitrates, statins, β-blockers, and antiplatelet agents, in addition to the Danshen extract treatment or placebo treatment. Because statins can have an effect of reducing Lp-PLA_2_ levels in a dose-dependent manner, all participants will receive atorvastatin 20 mg per night. If the patients are not suitable for receiving atorvastatin therapy, another isodose statin will be used. All treatments will be recorded in detail in the patients’ medical records as well as in their case report forms (CRFs).

Participants in the Danshen extract group will be treated using DanshenDuofensuanyan (200 mg per day) plus 0.9% saline injection (250 ml intravenously per day), whereas participants in the placebo group will be treated using placebo (glucose 200 mg per day) plus 0.9% saline injection (250 ml intravenously per day). If the patient has diabetes mellitus, glucose will be balanced with insulin. All of the included patients will undergo a 70-day treatment regimen during which patients in the Danshen extract group will receive a 10-day of course DanshenDuofensuanyan therapy in a double-blind manner and then continue to receive Danshen drop pills (a Danshen extract formulated for oral administration) unblinded, whereas the patients in the control group will receive standard medical care only. Study drugs will be provided by Shanghai Green Valley Pharmaceutical Co., Ltd. (Shanghai, China); however, they will not be involved in the design, patient recruitment, treatment, data collection and analysis, or any other procedures that would bias the study results.

A nitroglycerin tablet (0.5 mg per tablet, manufactured by Shanxi Yuanjingkangye Pharmaceutical Group Co., Ltd., Shanxi, China) is allowed if the patient has an angina attack, in which case the patients will be asked to record the administration times and the number of doses in detail, and the investigators will collect this information at the next follow-up visit. If the angina persists after three doses of nitroglycerin, the patient will be asked to go to the hospital for further treatment. If the patient has other underlying diseases, concomitant medications necessary to manage these disease are allowed and should be recorded in the medical records and CRFs. However, any other Chinese herbal medicines or Chinese patent medicines that have effects similar to Danshen are not allowed throughout the study period.

### Data management and monitoring

A CRF will serve as the repository for all results obtained in this trial. Source data will be traceable to the source documents (original records or certified copies). All data management procedures will be detailed in the trial-specific data management plan.

In addition, a data monitoring committee (DMC) will be established that will consist of an independent chair and two other independent members. The DMC will make sure that the protocol has been followed without deviation, including ensuring informed consent forms have been signed before inclusion, all inclusion and exclusion criteria are met, all primary and secondary variables and serious adverse events are well documented, and the source data and the CRFs are consistent.

### Statistical methods

The statistical analysis of this study will follow intention-to-treat principles. A blinded statistician will analyze the data using SAS version 9.1 software (SAS Institute Inc., Cary, NC, USA). Normally distributed data will be expressed as the mean ± SD. Numeric data will be expressed as percentages. *P* < 0.05 will be considered statistically significant. Repeated measures analysis of variance will be used for comparison of measurement data between the Danshen extract and control groups at baseline and 10 days and 70 days after treatment. Quantitative data will be compared using analysis of variance and *t* tests, whereas numeric data will be compared using the chi-square test.

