**Methods/design:**

This is a randomized, single-blind, placebo-controlled, adaptive clinical trial. A total of 156 patients meeting the eligibility criteria will be randomly assigned to either the Danshen extract (DanshenDuofensuanyan injection and Danshen drop spill) group or the placebo group in a 1:1 ratio. Participants will then undergo treatment with DanshenDuofensuanyan injection or placebo (glucose) during hospitalization, followed by open-label Danshen drop spill (30 pills/day) in Danshen extract group for 60 days after discharge. Because this is an adaptive trial, two interim analyses are prospectively planned. These will be performed after one-third and two-thirds of the patients, respectively, have completed the trial. On the basis of the results of these interim analyses, a data monitoring committee will determine how to modify aspects of the study without undermining the validity and integrity of the trial. The primary outcome measure is the serum level of Lp-PLA_2_ in the Danshen extract group and the placebo group. The secondary outcomes include the proportion of patients who show a clinically significant change, which is defined as at least a 20-point improvement in angina frequency score on the Seattle Angina Questionnaire and the carotid intima-media thickness, which will be measured using ultrasound. Other secondary efficacy and safety outcomes will also be assessed.

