### Research objectives

#### Primary objective

Serum levels of Lp-PLA_2_ will be assessed as baseline data as soon as the patients are included. After 10-day treatment during patients’ hospitalization, Lp-PLA_2_ levels will be assessed again on the day of discharge and on day 60 after discharge.

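### The planned repeated-measures ANOVA makes baseline Lp-PLA2 an outcome level and no deciding contrast is named; if the group main effect decides, a full treatment effect is diluted to two thirds

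*Protocol article*

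**What the plan says.** The Abstract defines the endpoint without a visit or a change score: "The primary outcome measure is the serum level of Lp-PLA_2_ in the Danshen extract group and the placebo group". The Primary objective section measures it at inclusion and adds that "Lp-PLA_2_ levels will be assessed again on the day of discharge and on day 60 after discharge". With a 10-day hospital course, these two later visits are days 10 and 70.

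The Statistical methods section states: "Repeated measures analysis of variance will be used for comparison of measurement data between the Danshen extract and control groups at baseline". The sentence goes on to the two later visits, so that the comparison in full is "between the Danshen extract and control groups at baseline and 10 days and 70 days after treatment". It then adds: "Quantitative data will be compared using analysis of variance and *t* tests". That sentence is tied to no endpoint and no visit. The threshold is P < 0.05, with sidedness not stated there.

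The sample size section assumes reductions of 30% and 10%, asks for at least 124 evaluable patients (one-sided alpha 0.05, power 80%) and recruits 156 to allow for 20% dropout. It gives no SD and no correlation between visits.

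**The concern.** Baseline is measured before treatment, so randomisation makes the expected group difference there zero. A model that treats it as a third outcome visit can use it badly or well, depending on which term is read:

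- The **group main effect** averages the treatment difference over a visit where there is none.
- The **group-by-time test** uses baseline as a reference but spends two degrees of freedom on an unspecific alternative.
- A **single-visit t test** ignores baseline altogether.

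The text admits all three for the only primary outcome and does not choose. A real effect could be missed by an inefficient test that was avoidable at no cost. The result could also depend on which test is treated as decisive after the data are seen. Two interim analyses with sample size adjustment are planned, so the choice should be fixed before any unblinded look.

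**Working it through.** **The plan's own figure.** The 124 is 62 per arm. It does not come from a comparison of means. The usual two-proportion formula with 0.30 and 0.10, two-sided, gives n = [1.960·√(2·0.2·0.8) + 0.842·√(0.3·0.7 + 0.1·0.9)]² / 0.2² = 61.6, so 62 per arm. The one-sided version, which is what the text states, gives 49 per arm, or 98. The stated 80% is therefore not tied to any test of Lp-PLA2 levels, and a starting point has to be assumed. I use two.

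**Assumptions (not in the document).** 62 per arm, unit variance at each visit, equal correlation rho between visits, two-sided 0.05, and the same effect δ (in SD units) at days 10 and 70 unless stated otherwise.

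- Scaling A sets the baseline-adjusted day-70 contrast to 80% power: δ = 2.802·√(2(1−rho²)/62), giving 0.480, 0.436 and 0.359 at rho 0.3, 0.5 and 0.7.
- Scaling B sets the unadjusted day-70 t test to 80% power: δ = 2.802·√(2/62) = 0.503.

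**Formulas.**

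- Group main effect: difference (0 + δ + δ)/3 = 2δ/3; variance per patient (1 + 2rho)/3; Z = (2δ/3)/√(2(1 + 2rho)/(3·62)); power Φ(Z − 1.96).
- Group-by-time: noncentrality λ = (62/2)·(2/3)·δ²/(1 − rho), on 2 and 244 df.
- Unadjusted day-70 t test: Z = δ/√(2/62).
- Baseline-adjusted day 70: Z = δ/√(2(1 − rho²)/62).

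**Results, full effect at both visits.**

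| Test | Scaling | rho 0.3 | rho 0.5 | rho 0.7 |
|---|---|---|---|---|
| Main effect | A | Z 2.44, 68% | Z 1.98, 51% | Z 1.49, 32% |
| Main effect | B | Z 2.56, 73% | Z 2.29, 63% | Z 2.09, 55% |
| Group-by-time | A | λ 6.80, 64% | λ 7.85, 70% | λ 8.90, 76% |
| Group-by-time | B | λ 7.48, 68% | λ 10.47, 83% | λ 17.44, 97% |
| Unadjusted day-70 t test | A | 76% | 68% | 52% |
| Unadjusted day-70 t test | B | 80% | 80% | 80% |
| Adjusted day 70 | A | 80% | 80% | 80% |
| Adjusted day 70 | B | 84% | 90% | 97% |

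**A comparison free of scaling.** For equal power, the main effect needs (9/4)·[(1 + 2rho)/3]/(1 − rho²) times the patients of the adjusted day-70 contrast: 1.3, 2.0 and 3.5 times at rho 0.3, 0.5 and 0.7.

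**Smaller effect at day 10.** With half the effect at day 10, the main-effect difference is (0 + δ/2 + δ)/3 = δ/2. Its power is 45%, 32% and 20% under A, and 48%, 40% and 35% under B.

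**Two visits, each at 0.05.** If days 10 and 70 were each tested and either could succeed, the chance of at least one false positive is about 9.5% at rho 0.3 and 8.4% at rho 0.7. The limit for independent tests is 1 − 0.95² = 9.75%.

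**The case against.** The strongest reply is that the Statistical methods section never says the group main effect decides. With baseline, day 10 and day 70 as levels, the group-by-time interaction is at least as natural a reading, and baseline does not dilute it. Repeated-measures ANOVA in a randomised trial is also valid, so the issue is efficiency and clarity, not bias. This stands, and it makes the dilution conditional.

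A reader might infer that the plan cuts power from 80% to 50% or less. The documents do not support that. It holds for one unselected test, and it depends on scaling, correlation and time course, none of which is given. Under scaling B with a full effect at both visits, the main effect reaches about 50% only at rho of roughly 0.8 to 0.9 (52% and 49%).

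Three further inferences also go too far:

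- **An 8% to 10% false-positive rate is planned.** The t-test sentence does not prescribe separate day-10 and day-70 tests of Lp-PLA2. The figure is what follows if both were run at 0.05.
- **Patients with a missing visit will be dropped, against the stated principle.** The section says "The statistical analysis of this study will follow intention-to-treat principles" and states no complete-case rule. Classical ANOVA software often works that way, but missing-data handling may be set out in a document not shown.
- **Statin status at entry is already available as a covariate.** The Treatment section says that treatments are recorded. Its statement that "another isodose statin will be used" concerns substitution during the study, not use before entry.

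The absence of a named contrast could likewise be cured in a full protocol or SAP. That does not remove the point, because making baseline a compared level is a choice the article states.

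**Conclusion.** The point holds in a conditional form. The article fixes baseline as one of three outcome levels and offers several tests without naming the one that decides. If the group main effect is used, a full effect at both later visits is diluted to two thirds. Under the assumptions above, its power is 68% to 32% (scaling A) or 73% to 55% (scaling B) over rho 0.3 to 0.7, and lower if the effect at day 10 is smaller. The group-by-time test escapes dilution but spends two degrees of freedom, with 64% to 76% or 68% to 97% over the same range. An unadjusted day-70 t test wastes the baseline: 76% to 52% where the adjusted contrast has 80%.

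These are ranges under assumptions, not properties of the plan. What does not depend on the scaling is the ranking of the main effect: with equal correlations and a full effect at both visits, it needs 1.3 to 3.5 times the patients of the baseline-adjusted day-70 comparison. The change is worth making before the first interim analysis.

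**What to change.** Replace the primary analysis sentence with a baseline-adjusted comparison of Lp-PLA2. This can be an ANCOVA, or a likelihood-based mixed model of days 10 and 70 with arm, visit, arm-by-visit and baseline Lp-PLA2 as covariate, using all randomised patients with a post-baseline value. Baseline should not be an outcome level, and no group comparison at baseline should count as a test of effect.

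Name one primary contrast, for example the arm difference at day 70. Day 10 is then secondary, or tested only if day 70 succeeds, which keeps the false-positive rate at the chosen level. State the sidedness with it.

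Two additions are optional. A log scale fits a trial sized on percentage reductions and would give a ratio of geometric means. Statin use at entry could be a covariate if it is recorded.

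The cost is analysis wording only, with no new data or visits. The small downside is committing to one time point.

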### Research objectives

#### Primary objective

Serum levels of Lp-PLA_2_ will be assessed as baseline data as soon as the patients are included. After 10-day treatment during patients’ hospitalization, Lp-PLA_2_ levels will be assessed again on the day of discharge and on day 60 after discharge.

#### Secondary objectives

The secondary outcomes are as follows:The proportion of patients in each treatment group who have clinically significant changes as defined by the angina frequency score on the Seattle Angina QuestionnaireCarotid arterial intima-media wall thicknessThe frequency of angina attacks per weekAngina grade according to the Canadian Cardiovascular Society Angina Grading ScaleConsumption of short-acting nitratesChanges in electrocardiogram resultsChanges in serum lipid levels, high-sensitivity C-reactive protein levels, and the rate of platelet aggregation

These outcomes will be assessed at the same time points as the primary outcome. The safety of Danshen extract therapy will be evaluated by the incidence of new-onset major vascular events, overall mortality, and incidence of severe and moderate hemorrhages during patients’ hospitalization and 60 days after discharge. After each interim analysis, the DMC will determine whether the study can continue or there is a need to modify or terminate the study.

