**Discussion:**

This study will provide evidence that Danshen extract is beneficial for stable angina and may establish a possible mechanism of Danshen treatment effects on cardiovascular disease. This study may also validate an objective blood test (LP-PLA_2_ level) for assessing the effectiveness of Danshen therapy in patients with stable angina pectoris.

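### The abstract promises evidence that Danshen benefits stable angina, but the primary outcome is a biomarker and no clinical outcome or visit is named to carry that claim

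*Protocol article*

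**What the plan says.** All places are in the protocol article.

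- **Conclusion.** The Discussion paragraph of the abstract states without qualification: "This study will provide evidence that Danshen extract is beneficial for stable angina".
- **Primary outcome.** Under Primary objective, the only measure is a blood marker. "Serum levels of Lp-PLA_2_ will be assessed as baseline data as soon as the patients are included", and "Lp-PLA_2_ levels will be assessed again on the day of discharge and on day 60 after discharge".
- **Secondary outcomes.** The list under Secondary objectives has at least nine efficacy items, counting lipids as one: SAQ angina-frequency responders, carotid intima-media thickness, weekly attacks, CCS grade, short-acting nitrate use, electrocardiogram changes, lipids, high-sensitivity C-reactive protein and platelet aggregation. On timing it says: "These outcomes will be assessed at the same time points as the primary outcome". That means two post-baseline visits, discharge (day 10) and 60 days later (day 70).
- **Threshold.** Statistical methods gives one rule, "P* < 0.05 will be considered statistically significant", and does not confine it to the primary outcome.
- **Tests.** "Repeated measures analysis of variance will be used for comparison of measurement data between the Danshen extract and control groups", across baseline, day 10 and day 70. In addition, "Quantitative data will be compared using analysis of variance and *t* tests, whereas numeric data will be compared using the chi-square test"; no visit is fixed for these.
- **Order.** The abstract mentions two secondary outcomes before the rest ("The secondary outcomes include the proportion of patients who show a clinically significant change", then carotid thickness), but not as a testing order.

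**The concern.** A difference in Lp-PLA2 does not show that patients with angina are better off. The article itself treats the marker as unproven for this purpose: both the abstract and the Discussion say the study may validate it as a measure of Danshen's effectiveness. The clinical sentence in the abstract therefore depends on the secondary outcomes, and the article does not say which one, at which visit, would justify it.

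Four of those outcomes bear directly on symptoms. With one threshold for all of them and none singled out, a reader of the results could take whichever one crosses 0.05 as the promised evidence, even if Lp-PLA2 does not differ. The clinical conclusion would then carry more than the usual risk of being a chance finding. The Lp-PLA2 analysis itself is not affected.

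**Working it through.** The article gives no family-wise error figure for the secondary outcomes, so there is nothing of its own to reproduce. The check asks how large the error would be if any one symptom outcome were allowed to carry the claim.

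**Inputs from the article.** Four symptom outcomes; two post-baseline visits; threshold 0.05. The article does not give the sidedness of that threshold for the analysis. I take it as two-sided, which is 0.025 in the direction favouring Danshen.

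**Assumed inputs.** Correlation ρ between outcomes of 0.2, 0.5 or 0.8; correlation 0.5 between visits; normal test statistics; no true effect on any of the four; no allowance for the two interim analyses.

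**Step 1: independence, as a reference.**
- Either direction: 1 − 0.95⁴ = 18.5%.
- Danshen's favour only: 1 − 0.975⁴ = 9.6%.

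**Step 2: four outcomes, one test each.** With a common correlation ρ, condition on a shared normal variable u:
- Either direction: 1 − ∫ φ(u) [Φ((1.96 − √ρ·u)/√(1−ρ)) − Φ((−1.96 − √ρ·u)/√(1−ρ))]⁴ du
- Danshen's favour: 1 − ∫ φ(u) [Φ((1.96 − √ρ·u)/√(1−ρ))]⁴ du

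| ρ between outcomes | Either direction (nominal 5%) | Danshen's favour (nominal 2.5%) |
|---|---|---|
| 0.2 | 18.0% | 9.1% |
| 0.5 | 15.6% | 7.8% |
| 0.8 | 11.4% | 5.7% |

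In Danshen's favour this is 5.7/2.5 = 2.3 to 9.1/2.5 = 3.6 times the nominal rate.

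**Step 3: the same four tested separately at both visits (eight tests).** The correlation matrix is the Kronecker product of the outcome matrix and a two-by-two visit matrix with 0.5 off the diagonal; 1,000,000 simulated draws.

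| ρ between outcomes | Either direction | Danshen's favour |
|---|---|---|
| 0.2 | 30.9% | 15.9% |
| 0.5 | 26.8% | 13.5% |
| 0.8 | 20.0% | 10.0% |

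This is an upper case, because repeated measures analysis of variance is planned for measurement data. That does not call for a separate test at each visit.

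**Step 4: a reading between the two.** Suppose SAQ responders and CCS grade are tested by chi-square at each visit, and attacks and nitrate use by one across-visit test each. That makes six tests. For ρ of 0.2, 0.5 and 0.8 the rates are 24.8%, 21.7% and 16.9% in either direction, and 12.7%, 10.9% and 8.5% in Danshen's favour. They lie between steps 2 and 3.

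**Step 5: sidedness.** The sample size section uses a one-sided 0.05. If the 0.05 in Statistical methods were also one-sided, replacing 1.96 by 1.645 in the second formula of step 2 gives 17.2%, 14.4% and 10.6% in Danshen's favour, against a nominal 5%.

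**The case against.** **Is this only detail left to an analysis plan?** A multiplicity rule for secondary outcomes is commonly placed in the full protocol or SAP, and neither is shown. That stands: the missing rule is not the finding. The finding is what the article does state, namely an unqualified clinical conclusion, a biomarker as the only primary outcome, and one general threshold with no clinical outcome or visit attached to the conclusion. An SAP could add a rule, but the abstract's sentence would still have to match it.

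**Is the abstract's sentence a decision rule?** No, and this also stands. Nowhere does the article say that one significant symptom outcome counts as benefit. Its stated aim concerns Lp-PLA2, and the main Discussion is more guarded about what the results may show. The error rates are therefore conditional on such a reading.

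**A stronger reading.** A reader might infer that all nine outcomes are tested at two visits: 18 tests, with a chance of a false positive of 40% at a common correlation of 0.5, or 1 − 0.95¹⁸ = 60% if independent. The documents do not support this:
- They say the outcomes are assessed, not tested, at each visit.
- Repeated measures analysis of variance is planned for measurement data.
- Lipids, C-reactive protein, platelet aggregation and carotid thickness are laboratory or surrogate measures. They could no more carry an angina claim than Lp-PLA2 can.
- Those percentages count results in either direction, whereas the claim concerns benefit.

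**Does error control settle the matter?** No. After discharge the Danshen group takes open-label drop pills and controls receive standard care only. Symptom reports at day 70 are open to bias that no alpha rule removes, so the choice of visit matters as well as the choice of outcome.

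**Conclusion.** The point holds in a limited form. The abstract's clinical conclusion cannot follow from the primary outcome, and the article does not name the clinical outcome and visit that would support it. If any of the four symptom outcomes were taken as sufficient, a false result in Danshen's favour would occur in about 6% to 9% of trials with one test each, and in 10% to 16% if each were tested at both visits, against a nominal 2.5%. The two-sided counterparts are 11% to 18% and 20% to 31%, against 5%.

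All correlations are assumed, the threshold is taken as two-sided, and the two-visit figures are an upper case. These outcomes address the same symptom burden, which suggests fairly high correlation and hence the lower end of each range. Even there the rate is a little over twice nominal.

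**What to change.** Choose one of two changes before any outcome results are seen, including those of the first interim analysis.

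1. **Narrow the conclusion.** Reword the abstract so that it claims evidence about Lp-PLA2 only. This is the minimum change.
2. **Name what carries the clinical claim.** Specify one key secondary outcome at one visit, for example the SAQ angina-frequency responder proportion (already listed first), preferably at discharge while patients are still blinded. Test it only if the primary Lp-PLA2 test succeeds, at a stated two-sided alpha that fits the interim plan. Report the other secondary outcomes and visits as exploratory estimates with confidence intervals. Claim benefit in angina only if this test succeeds. If day 70 is chosen instead, state that the comparison after discharge is open-label.

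Neither change needs extra patients, visits or data. Under the second, nominally significant results on the other secondary outcomes can no longer be presented as proof of benefit. A discharge comparison covers only the 10-day injection phase and says nothing about the oral phase. The article gives no assumed SAQ responder rates, so the power of the key secondary test cannot be judged from it.

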**Fig. 1 Fig1:**
[figure not shown]
Flowchart of the trial

**Table 1 Tab1:** Inclusion and exclusion criteria

Inclusion criteria	Exclusion criteria
1. Aged 18–75 years 2. Written informed consent provided 3. Patients with a clinical diagnosis of chronic stable angina who fulfill one of the following conditions: a. Symptoms that support the diagnosis of chronic angina, and/or a history of an abnormal exercise response limited by angina, and/or electrocardiographic changes b. A history of myocardial infarction and ST-T changes c. Stenosis greater than 50% in at least one major epicardial coronary artery, as shown by coronary angiography or computed tomographic angiography d. Coronary heart disease confirmed by radionuclide angiocardiography 4. Patients with moderate angina pectoris, which is defined as grade II or III on the Canadian Cardiovascular Society Angina Grading Scale	1. Patients with severe complications that would complicate the condition, as assessed by the investigator, including liver or renal dysfunction, severe cardiopulmonary dysfunction, pulmonary hypertension, chronic obstructive pulmonary disease, a history of epilepsy, or cerebral hemorrhage 2. Patients who experienced myocardial infarction or who were classified as grade IV on the Canadian Cardiovascular Society Angina Grading Scale within the preceding 3 months 3. Patients with chest pain that is caused by any other disease (e.g., acute myocardial infarction, severe neurosis, menopausal syndrome, or hyperthyroidism) 4. Patients with a history of drug-induced bleeding or a history of bleeding caused by warfarin 5. Patients with a history of hematopoietic disorder 6. Patients who have had surgery within the previous 4 weeks or who have a hemorrhagic tendency 7. Women who are pregnant or lactating or who have a positive pregnancy test, or women who have a menstrual period at baseline 8. Patients who are participating in other trials or who have participated in other trials within the past 3 months 9. Patients with a history of allergy or with a known or suspected allergy to the study drug 10. Patients with a known or suspected history of alcohol or drug abuse within the past 2 years 11. Patients with a mental disorder 12. Family members or relatives of the study center staff 13. Inability to adhere to study procedures

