**Fig. 2 Fig2:**
[figure not shown]
The schedule of enrollment, interventions, and assessments. *Blood RT* Blood routine test, *Echo* Echocardiography, *EKG* Electrocardiography, *IMT* Carotid intima-media thickness, *Lp-PLA*
_*2*_ Lipoprotein-associated phospholipase A_2_

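### The stated safety evaluation has no place for non-serious hypersensitivity or infusion reactions or mild bleeding, although Table 1 treats study-drug allergy and bleeding history as reasons for exclusion

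*Protocol article*

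**What the plan says.** Under Secondary objectives, the protocol article says that the safety of the therapy will be evaluated by the "incidence of new-onset major vascular events, overall mortality, and incidence of severe and moderate hemorrhages". The observation period is given as "hospitalization and 60 days after discharge. After each interim analysis", and the second of those sentences goes on to have the DMC decide on continuing, modifying or terminating the study.

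Two other places touch on safety:

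- The Methods/design part of the abstract states: "Other secondary efficacy and safety outcomes will also be assessed". It names none of the safety outcomes.
- Data management and monitoring lists among the DMC's tasks ensuring that "all primary and secondary variables and serious adverse events are well documented".

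The exclusion criteria in Table 1 include "Patients with a history of allergy or with a known or suspected allergy to the study drug" and "Patients with a history of drug-induced bleeding or a history of bleeding caused by warfarin". The Treatment section gives the Danshen arm a daily intravenous infusion for 10 days, then open-label oral pills. The control arm has a placebo infusion and then standard care alone. Antiplatelet agents are part of the background therapy in both arms.

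**The concern.** A sentence that says how safety will be evaluated is a definition, and this one sets a severity threshold for bleeding at moderate. It has no component for allergic or infusion reactions and none for adverse events overall. These are plausible concerns for an infused herbal extract, and the protocol's own eligibility criteria show caution about two of them: allergy to the study drug and a tendency to bleed on drugs. The platelet aggregation rate is also a secondary outcome, so an effect on platelets is of interest while the mildest clinical bleeding is left out of the safety count.

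The trial could therefore report no safety difference between the arms while an excess of non-serious reactions or mild bleeds stood outside the comparison. The Discussion presents randomized trials as the standard for judging both efficacy and safety of a Chinese medicine, so a safety statement from this trial is foreseeable.

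**Working it through.** The article gives no safety figure to reproduce. The check is mainly a comparison of texts, with a short calculation for scale.

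**Step 1: does each type of event enter the stated safety evaluation?**

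| Event | In the Secondary objectives list? | Covered elsewhere in the article? |
|---|---|---|
| Major vascular event, death | Yes | – |
| Moderate or severe bleeding | Yes | – |
| Mild bleeding, non-serious | No | Not stated |
| Hypersensitivity or infusion reaction, non-serious | No | Not stated |
| Other serious adverse event | No | Documented under DMC oversight; no analysis stated |

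**Step 2: do the other two safety statements fill the gap?** The abstract sentence comes before any safety outcome has been named. It can be read as pointing to the Secondary objectives list or as adding to it; on either reading it names nothing. The monitoring statement is about records and concerns serious events, so it gives a non-serious reaction no place in the result.

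**Step 3: which exclusions bear on the omitted events?** Study-drug allergy bears directly on hypersensitivity. A history of drug-induced bleeding bears on bleeding; the criterion carries no severity grade.

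**Step 4: which period is placebo-controlled?** By the Treatment section, only the infusion period, up to discharge at about day 10. After that, open-label pills are compared with standard care alone, and the Discussion concedes that patients cannot be blinded after discharge.

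**Step 5: scale.** From Statistical hypotheses and sample size determination, 156 patients at 1:1 give 156/2 = 78 per arm, and 124 before the dropout allowance gives 124/2 = 62. The chance of at least one case in an arm of n patients with true incidence p is 1 − (1 − p)^n. The incidences are assumptions, because the article gives none.

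| Assumed p | n = 78 | n = 62 |
|---|---|---|
| 1% | 0.54 | 0.46 |
| 2% | 1 − 0.98^78 = 0.79 | 0.71 |
| 5% | 1 − 0.95^78 = 0.98 | 0.96 |

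Reactions at these rates would more likely than not occur in the Danshen arm, except at 1% with 62 patients. If non-serious, each would add zero to the stated safety result. The table shows the chance of seeing a case. It says nothing about power to detect a difference between arms.

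**The case against.** The strongest objection is that this is a condensed article. It points to a full protocol on the registry, a separate data management plan and a schedule in Fig. 2 whose content is not shown. Routine adverse-event collection commonly sits in such documents. The safety sentence does not claim to be exhaustive, and the abstract allows for other safety outcomes. This stands to the extent that nobody can conclude from the article that non-serious events will go unrecorded. It does not remove the point: the article states a definition of the safety evaluation, and fuller collection elsewhere would still have to be reconciled with it.

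A reader might also infer more than the text supports:

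- **That Table 1 screens for liver or kidney reactions or for mild bleeding.** It does not. The criterion reads "Patients with severe complications that would complicate the condition, as assessed by the investigator, including liver or renal dysfunction", so these are pre-existing conditions, listed with others such as epilepsy. Mild bleeding is not named.
- **That the DMC looks at serious adverse events only.** Its list of tasks is introduced as examples and includes all primary and secondary variables. The article does not say which data the DMC sees at an interim analysis.
- **That events in the two periods are pooled.** The text names both periods and does not say how they are combined.
- **That the listed events are all rare and severe.** Moderate bleeding is included, and no event rates are given.

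It is also fair to say that the point leaves the primary outcome, the Lp-PLA2 level, and its analysis untouched.

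**Conclusion.** The concern holds in a limited form. The safety evaluation, as defined under Secondary objectives, does not count non-serious hypersensitivity or infusion reactions or mild bleeding. The allergy and bleeding-history exclusions and the daily infusion on top of antiplatelet agents make those events relevant, and neither the abstract nor the monitoring section brings them in.

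The size is illustrative. At assumed incidences of 2% and 5%, at least one case among 78 Danshen patients has probability 79% and 98%, falling to 71% and 96% with 62. The conclusion rests on the article's definition being applied as written; the full protocol could supply broader collection, which keeps confidence moderate. It is a change that should be made because it is cheap and strengthens any safety statement.

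**What to change.** Amend the safety sentence under Secondary objectives so that:

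1. Safety is the incidence of all adverse events by arm, serious and non-serious.
2. Hypersensitivity or infusion reactions, and bleeding of any grade, are named categories.
3. The events now listed are kept as a subset.
4. The blinded infusion period (to discharge, about day 10) is reported separately from the open-label oral period, because only the former is placebo-controlled.
5. This table is part of the data given to the DMC at each interim analysis.

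If the full protocol already collects these events, align the article's wording with it and name the safety outcomes that the abstract refers to.

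The cost is a change of wording, adverse-event entries in the case report form at visits already planned, and one more table. No visit or procedure is added.
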